Participants will have up to 48 h to consider their participation in the study. Upon expressing interest, they will be provided with sufficient time to review and complete a consent form, followed by the assessment tools. The assessments will be administered by trained members of the research team at the participant's preferred location and conducted in their preferred language. While most assessments are self-report measures, the research team will be available to provide assistance to participants who prefer an interview-style format. This is particularly important for questions that may be complex to interpret or could elicit emotional responses. In addition, the research team will have access to support from mental health professionals at ALERT Hospital and the ENAPAL, if needed, during the screening process.

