##### 2.3.1.8. Feasibility and Acceptability Indicators

The study will monitor the recruitment rate, including the number of patients referred and the proportion who consented out of all eligible individuals with leprosy referred from recruitment sites or through self-referrals, as well as the attrition rate, which is the number of participants withdrawn compared to those who consented.

The study will evaluate the feasibility of administering the baseline and outcome exploratory assessment battery, focusing on randomization, blinding procedures, and the ability to perform a sample size calculation based on the feasibility data.

The evaluation will assess the number of participants recruited and randomized, session attendance, reported adverse effects, assessment measure acceptability, and the potential for future site. Acceptability will be measured using the TFA scale [41, 42], assessing researchers' and participants' perceptions of the intervention's appropriateness.

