### 2.4. Data and Management

Summary statistics, means, medians, counts, and percentages along with corresponding measures of variability will be reported, along with 95% confidence intervals. The information gathered on the variability of the outcome measures will be sufficient to allow a formal sample size calculation to be made for the subsequent definitive RCT. The proportion of participants recruited and retained in the study will be reported along with 95% confidence intervals. A sample size of 100 will allow the recruitment/retention rates to be estimated with an accuracy of ± 8%.

One-way repeated measures analysis of variance to elucidate the impact of interventions on scores on all outcome tools while accounting for baseline characteristics of participants such as age, gender, and baseline severity of psychological symptoms will be employed. Mean and SD and effect sizes calculated as Cohen's d noted in this trial will inform sample size calculation for future definitive trials. The project will also have a clear Stop-Go criterion:• If the retention rate is 70% or higher, we will proceed with the full RCT as it is feasible.• If the retention rate is between 50% and 70%, we will explore methods to increase the retention rate to the required 70%. Alternatively, we may increase the required sample size to account for the higher drop-out rate.• However, if the recruitment rate is less than 50%, a full trial may not be feasible. In such cases, alternative approaches will be considered.

Subgroup analysis will be carried out with respect to age, duration of illness, number of previous episodes, and gender by adding a treatment with covariate interaction into the primary analysis model.

Data will be initially stored in a secured office location and subsequently digitized for storage on a secure network. In addition, all project-generated data will be assigned unique codes to protect participant confidentiality. Data associated with these codes and any identifiable information will be stored separately.

Descriptive statistics will be conducted for baseline and postintervention measures, including mean scores, standard deviations, and ranges. In addition, recruitment, attendance, and dropout rates will be reported to assess feasibility and acceptability.

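### The Stop-Go rule grades retention in its first two steps and recruitment in its third, so three of six combinations of the two rates get no verdict or two

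*Protocol article*

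**What the plan says.** Section 2.4 (Data and Management) of the protocol article introduces the rule with the words "The project will also have a clear Stop-Go criterion" and lists three bullets.

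- First: "If the retention rate is 70% or higher, we will proceed with the full RCT as it is feasible".
- Second: "If the retention rate is between 50% and 70%, we will explore methods to increase the retention rate to the required 70" per cent. Enlarging the sample to allow for the losses is offered as the alternative.
- Third: "However, if the recruitment rate is less than 50%, a full trial may not be feasible". Other approaches would then be considered.

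Section 2.3.1.8 (Feasibility and Acceptability Indicators) describes the two rates separately. Recruitment includes "the proportion who consented out of all eligible individuals with leprosy referred from recruitment sites or through self-referrals". Loss after entry is "the attrition rate, which is the number of participants withdrawn compared to those who consented". Section 2.4 likewise promises to report the proportions recruited and retained, with confidence intervals.

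**The concern.** The three bullets read as one ladder with cut-points at 70% and 50%, but the lowest rung measures something else. Poor retention, the result that a retention rule most needs to catch, never triggers a stop on its own account. Poor recruitment can trigger a doubtful verdict while good retention triggers a firm go.

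The trial exists to assess feasibility and to inform a definitive trial (section 1, Introduction; section 3, Discussion), and this is the only progression rule with thresholds that the article gives. If its meaning is left open until the rates are known, the same data could support either decision, depending on which reading is chosen.

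**Working it through.** This is a check of logic. The plan has no figure to reproduce here.

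**Inputs (section 2.4).** Let S be the retention rate and R the recruitment rate.

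1. If S ≥ 70%: go.
2. If 50% ≤ S < 70%: amend. I assign exactly 70% to the first step only, since that step says 70% or higher.
3. If R < 50%: doubtful.

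**Are S and R the same quantity?** No. By section 2.3.1.8, R is those who consented divided by the eligible people referred or self-referred. Attrition concerns people lost after consent. A trial can be high on one and low on the other.

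**The rule as written, over three bands of S and two of R:**

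| Retention | Recruitment ≥ 50% | Recruitment < 50% |
|---|---|---|
| ≥ 70% | go | go **and** doubtful |
| 50% to < 70% | amend | amend **and** doubtful |
| < 50% | **no verdict** | doubtful (through recruitment only) |

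Cells with exactly one verdict: 3. Cells with two: 2. Cells with none: 1. So 2 + 1 = 3 of 6 cells fail.

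**The same check at specific values.** Take S and R each at 80%, 60% and 40%, which gives nine pairs.

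- S = 80%, R = 40%: go and doubtful.
- S = 60%, R = 40%: amend and doubtful.
- S = 40%, R = 60% or 80%: no verdict.
- The other five pairs: one verdict each.

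That is 2 pairs with two verdicts, 2 with none and 5 with one.

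**The rule with retention in the third step.** S = 80% gives go, S = 60% gives amend and S = 40% gives doubtful, whatever R is. All nine pairs then have exactly one verdict. Recruitment would no longer have any threshold.

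**The case against.** **It is an obvious slip of one word.** The adjoining cut-points at 70% and 50% do point that way. But the document cannot settle it: recruitment is itself a stated feasibility parameter (sections 1, 2.1 and 2.3.1.8), so a recruitment floor would be a sensible thing to intend. A slip would also still leave the published stop step wrong.

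**The third bullet opens with a contrast word and is worded softly, so it may qualify the first two.** If recruitment below 50% overrides the other steps, the two double-verdict cells are resolved. The article does not state that precedence, and the first bullet is firm, not advisory. Even with the override, retention below 50% with recruitment of 50% or more has no verdict, so one of the six cells still fails.

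**An article leaves such detail to the full protocol or the analysis plan.** That would answer an omission. Here the rule is stated, and the statement does not work when followed.

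**The rule touches no participant and no analysis in this trial.** This is true, and it limits the consequence to the decision about the later trial. Other feasibility information, such as attendance, adverse effects and acceptability of the measures, will also inform that trial's design.

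**A single recruitment floor is a legitimate gate.** This stands. Recruitment does not need go and amend bands of its own, and their absence is not a fault.

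**Conclusion.** The third step of the Stop-Go rule uses a different rate from the first two, and the rule read literally fails in three of six combinations: one has no verdict and two have two. The count is of cells in a logical grid. It says nothing about how likely each result is, and it rests only on the bullets as printed and on the separate descriptions of the two rates.

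Three stronger readings are not supported.

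- A reader might infer that retention below 50% never gets a verdict. It does get one when recruitment is also below 50%, though only because of recruitment.
- A reader might infer that the third bullet certainly should say retention. The cut-points suggest it, but nothing in the document confirms it.
- A reader might infer that retention is one minus withdrawals over those who consented, and that this base could lift a poor result above 70%. The article defines attrition that way but never equates retention with its complement. Section 2.4 ties the precision of both rates to the sample of 100, the number randomised in section 2.1. Whether people could consent before their eligibility is settled is also unclear. The documents give no figure from which such an effect could be sized.

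**What to change.** Before any recruitment or retention results are known, confirm which rate the third bullet of section 2.4 was meant to use, and amend it accordingly.

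- **If retention was meant:** replace recruitment with retention in that bullet, and word the bands as 70% or higher, 50% to below 70%, and below 50%. Every result then gets one verdict. Recruitment would be reported without a progression threshold, which the sponsor should accept knowingly.
- **If recruitment was meant:** keep it, add a verdict for retention below 50%, and state which rate takes precedence when the two disagree.

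If a fuller protocol already carries the intended wording, bring the article into line with it. The cost is a few words, with no change to recruitment, assessments or sample size.

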## 3. Discussion

Leprosy not only leads to physical disabilities but also significantly impacts the mental health of affected individuals. The psychosocial consequences of leprosy are profound, with numerous studies highlighting a high prevalence of mental health disorders among those affected [12, 44]. Persons affected by leprosy often experience multiple traumas from the point of diagnosis onwards, contributing to a high prevalence of mental health comorbidities. They also endure stigma, which is not merely a social inconvenience [9, 45, 46]. Furthermore, the mental health burden extends beyond individuals directly affected by leprosy; family members, particularly children of leprosy-affected parents, also experience significant mental health challenges, as they often take on caregiving roles and face societal stigma themselves [3]. Finally, the mental health implications of leprosy are also compounded by socioeconomic factors [47]. Individuals with leprosy frequently have lower educational attainment and income levels, which are associated with poorer mental health outcomes [48–50]. The presence of physical disabilities resulting from leprosy can also lead to chronic pain, which has shown to correlate with increased psychological distress [51]. As noted by many individuals affected by leprosy have become accustomed to societal prejudice, leading to a reluctance to assert their rights and seek help, which further perpetuates their mental health struggles [46].

In Ethiopia, where leprosy remains endemic, despite the efforts there is still a significant gap in addressing the mental health needs of these individuals. This gap is particularly evident in the lack of evidence-based interventions specifically tailored to alleviate the psychological impact of leprosy as mental health care for leprosy patients is generally inconsistent, varying based on available resources and may include counseling and medication. Unfortunately, such services are often limited in rural areas where there is a shortage of skilled professionals and diagnostic expertise.

By offering support that is sensitive to the cultural and social context of the participants, these interventions can help individuals cope more effectively with the challenges posed by the disease, thereby enhancing their quality of life.

The present trial is designed to evaluate the feasibility and acceptability of the TSR for individuals with lived experience of leprosy in Addis Ababa, Ethiopia. The TSR aims to reduce symptoms of PTSD, anxiety, and depression while enhancing social support and overall mental health. This trial will assess whether the TSR is a viable and effective intervention for this population, and whether it can be implemented in a culturally sensitive manner that addresses the unique challenges faced by individuals with leprosy.

This trial has several limitations. First, challenges related to stigma and social isolation might pose difficulties in recruitment and participant engagement, potentially leading to a biased sample. Second, the relatively small sample size may limit the generalizability of the results. Third, the absence of a long-term follow-up may limit the understanding of the sustained effects of the intervention. Despite these limitations, this trial will provide valuable insights into the feasibility of implementing culturally adapted mental health interventions for individuals affected by leprosy. The inclusion of qualitative interviews will further enhance our understanding of the participants' experiences and inform the design of future RCTs aimed at evaluating the effectiveness of the TSR. Most importantly, the strength of the current study is in its potential to ensure there is a sustainable, stigma-friendly response beyond the project as it includes not only professionals but also nonspecialist peer supporters with lived experience in TSR.

In conclusion, this trial represents an important step toward improving mental health care for individuals affected by leprosy. By evaluating the feasibility of the TSR in a culturally sensitive context, this study will contribute valuable knowledge to the field and lay the groundwork for future research on effective mental health interventions for marginalized populations and/or for people affected by NTD. The findings from this trial are expected to provide critical insights into how culturally adapted interventions can be used to support the psychological well-being of individuals living with leprosy, ultimately paving the way for future RCTs.

## Figures and Tables

**Table 1 tab1:** Design of the planned intervention.

	Study period			
	Enrollment	Baseline assessment	The intervention	Postintervention assessment
	−*t*1	*t*0	4 sessions	*t*1
Enrollment:				
Eligibility screen	X			
Informed consent	X			
Intervention: TSR				
Assessments:				
Sociodemographic Questionnaire		X		
International Trauma Questionnaire (ITQ)		X		X
Generalized anxiety disorder 7-item (GAD-7)		X		X
Patient Health Questionnaire-9 (PHQ-9)		X		X
Health Questionnaire (EQ-5D-5L)		X		X
Oslo Social Support Scale (OSSS-3)		X		
5-Question stigma indicator—affected people		X		
TFA Acceptability Questionnaire				X
Qualitative interview				X

## Data Availability

The data that support the findings of this study are available on request from the corresponding author. The data are not publicly available due to privacy or ethical restrictions.
